## Methods/design

The protocol of this pCRN study is presented in accordance with the 2013 SPIRIT (Standard Protocol Items: Recommendations for Interventional Trials) Statement (see Additional file 1 for the populated SPIRIT Checklist and Table 1 for the trial schedule of enrollment, interventions, and assessments in accordance with recommended SPIRIT figure).

**Table 1 Tab1:** Time points of each assessment index

	Study period										
Time point	Enrollment	Allocation	Active treatment post allocation						Follow-up		
	Week −1	Week 0 (Baseline)	Week 1	Week 2	Week 3	Week 4	Week 5	Week 6	Week 7	Week 10	Week 14
Enrollment											
Eligibility screening	○										
Written informed consent	○										
Vital signs	○								○	○	○
Sociodemographic characteristics, medical history (e.g., LBP, medication history)	○										
Physical examination	○										
Randomized allocation		○									
Interventions											
Treatment in CMT group			←2–3 times/week →				←1–3 times/week →				
Treatment in UC^a^ group (times/week)			←2–3 times/week →				←1–3 times/week →				
Treatment in CMT + UC^a^ group (times/week)			←2–3 times/week →				←1–3 times/week →				
Assessments											
Symptoms and change in medicine		○		○	○	○	○	○	○	○	
NRS of LBP and leg pain	○	○		○	○	○	○	○	○	○	○
ODI		○					○		○	○	
PGIC							○		○	○	
ROM		○					○		○	○	
EQ-5D		○					○		○	○	○
HUI-III		○					○		○	○	○
Economic evaluation		○					○		○	○	○
Adverse events		○	← every visit →						○	○	○

*CMT Chuna* manual therapy, *UC* usual care, *NRS* Numeric Rating Scale, *LBP* low back pain, *ODI* Oswestry Disability Index, *PGIC* Patient Global Impression of Change, *ROM* range of movement, *EQ-5D* EuroQol-5 dimensions, *HUI-III* Health Utility Index III

^a^UC: medication will be administered daily and physical therapy will be applied 2–3 times/week

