### Sample size

Determination of study sample size for pCRN: the following assumptions were made for calculation of valid sample size based on previous literature: (1) level of significance (*α*) = 0.05, (2) type 2 error (*β*) = 0.2; with test power set at 80% and (3) referring to NRS difference from prior Korean medicine research using the NRS as the primary measure [32, 33], and average difference and standard deviation (SD) between the three groups specified as 1.5 and 2.5, respectively, by a designated statistician, (4) compliance was set as 80%.

G*Power 3.1.7 was used for sample size calculation, and based on (3) and applied values of mean ± SD, the derived effect size was 0.49. Consequent sample size, as determined by (1) and (2), and applying acquired sample size, was 45 (15 per group).

These results imply that to test the above hypotheses and factoring in a dropout rate of 25%, each group requires a minimum 15 × 100/75 ≒ 20 (subjects), resulting in a total 60 participants.

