### Statistical analysis

Intention-to-treat (ITT) analysis will be the primary analysis used for all subjects who receive one or more treatment sessions, and additional per-protocol analysis will be performed in subjects who complete clinical trial participation, excluding dropouts. The primary endpoint will be at 1 week following the end of treatment (7 weeks post random allocation). Continuous data will be analyzed with a paired *t* test for pre-post within-group difference and with an independent *t* test for group comparison between *Chuna* and usual care if normally distributed, and the Wilcoxon rank sum test if not. For comparing between the three groups of *Chuna* with usual care, *Chuna*, and usual care, if continuous data satisfies the normality test, analysis of variance (ANOVA) will be used to test between-group difference, and the Kruskal-Wallis test if it does not. *Chuna* with usual care versus *Chuna*, and *Chuna* with usual care versus usual care will be analyzed using Duncan’s post-hoc test. Post-hoc analysis of non-normally distributed data will use the Wilcoxon rank sum test with significance level adjusted by the Bonferroni test. Categorical data will be analyzed using the chi-square test or Fisher’s exact test. A paired *t* test will be used in pre-post within-group differences by time point. Secondary analyses will include analysis of covariance (ANCOVA) adjusting for statistically significant between-group differences in baseline outcomes or covariant factors at baseline, and subgroup analyses by LBP disease differentiation (nonspecific LBP, lumbar intervertebral disc herniation, and spinal stenosis), pain duration (subacute, chronic, and hyperchronic), and main site of pain (LBP worse than leg pain, and LBP less than leg pain) to explore the feasibility of a large, multicenter, pragmatic RCT.

All statistical analysis will use a two-tailed test as a principle, and significance level will be set at 5%. In addition, last observation carried forward (LOCF) will be conducted to handle missing data as it is currently widely used in clinical trials.

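### LOCF is the only stated missing-data method, with 25% dropout allowed for; it can bias the week-7 pain comparison in a size and direction set by who leaves and when

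*Protocol article*

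**What the plan says.** The Statistical analysis section states that "last observation carried forward (LOCF) will be conducted to handle missing data as it is currently widely used in clinical trials". The primary analysis set is everyone who had at least one session, and the primary time point is week 7. A further per-protocol analysis leaves dropouts out.

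The Sample size section reaches its total by "factoring in a dropout rate of 25" per cent. It gives no timing of dropout, no reasons for it and no split by arm.

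The Table 1 row "NRS of LBP and leg pain" shows scores at screening, at week 0, at each of weeks 2 to 6, and at weeks 7, 10 and 14. There is none at week 1. Entry requires an average NRS of at least 5 (Inclusion criteria). Physicians and participants know the allocation (Blinding).

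**The concern.** LOCF assumes that a participant's pain would have stayed at its last recorded level until week 7. All three arms are treated for six weeks from a high entry score, so pain is expected to fall, and the assumption is poor for anyone who leaves early. The clearest case is a participant treated once and lost before week 2. That person belongs to the primary analysis set but has only screening and baseline scores to carry forward.

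Participants know their treatment, so dropout may plausibly differ between arms. LOCF then turns part of that difference into an apparent treatment difference. The filled scores are also analysed as though they had been observed.

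Two uses of the result are affected: the test of comparative effectiveness, and the fallback aim of sizing the full trial from these data. The only support offered for the method is that it is common.

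**Working it through.** **1. The plan's own figures.** The inputs are in Sample size: "level of significance (*α*) = 0.05", "with test power set at 80" per cent, and "average difference and standard deviation (SD) between the three groups specified as 1.5 and 2.5, respectively". Three means spaced 1.5 apart with SD 2.5 give f = √((1.5² + 0² + 1.5²)/3)/2.5 = 0.490, matching the stated 0.49. One-way ANOVA with 45 participants has power 0.818, and with 42 it has 0.786, so 45 is reproduced. Dropout inflation gives 15/0.75 = 20 per group, or 60 in total. At the planned rate, 0.25 × 60 = 15 week-7 values could be filled.

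**2. Illustration by hand.** Assumptions not in the document: a 3-point linear fall from week 0 to week 7, and dropouts' last scores spread evenly over the visits at weeks 0, 2, 3, 4, 5 and 6.

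- Mean last visit: (0 + 2 + 3 + 4 + 5 + 6)/6 = 20/6 = 3.33 weeks.
- Overstatement of week-7 pain per dropout: 3 × (1 − 3.33/7) = 1.57 points.
- True difference 1.5, growing linearly, 25% dropout in each arm: 0.75 × 1.5 + 0.25 × 1.5 × 3.33/7 = 1.125 + 0.179 = 1.30.
- No true difference, dropout 15% versus 35% (3 versus 7 of 20): 0.20 × 1.57 = 0.31, against the arm with more dropout.
- No true difference, 10% versus 40% (2 versus 8 of 20): 0.30 × 1.57 = 0.47.
- No true difference, equal dropout: 0.

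**3. Simulation of a two-arm comparison.** This used 20 per arm and SD 2.5. Further assumptions: baseline mean 6.5, within-person correlation 0.5 + 0.5 × 0.7^lag, and linear or early-plateau improvement.

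| Dropout pattern | True difference | LOCF estimate |
|---|---|---|
| Unrelated to pain, 25/25%, early | 1.5 | 1.18–1.24 |
| Same, spread evenly | 1.5 | 1.30–1.40 |
| Same, late | 1.5 | 1.41–1.48 |
| Unrelated to pain, 15/35% or 35/15% | 1.5 | 0.70–1.65 |
| Rising with pain, 25/25% | 1.5 | 1.20–1.23 |
| Rising with pain, 15/35% or 35/15% | 1.5 | 0.65–1.76 |
| Rising with pain, 15/35% | 0 | 0.48–0.58 |

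In the last row LOCF rejects in 7–9% of runs. When dropout rises with pain, a likelihood-based repeated-measures model gives 1.46–1.53 for a true 1.5, with about 95% coverage. With no true difference it gives about 0 and about 5% rejection. That comparison favours the model somewhat, because its covariance was taken as known and dropout depended only on observed scores.

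**4. Standard error.** The full-data value is 2.5 × √(2/20) = 0.79.

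- Dropout unrelated to pain: LOCF's standard error is 0.79–0.86, against 0.91–0.92 for complete cases. It matches the actual spread of the LOCF estimate.
- Dropout rising with pain: LOCF's standard error is 0.94–1.00, larger than the model's 0.87. Coverage is 0.87–0.95, and the shortfall comes from bias.

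**The case against.** - **The bias is not automatic.** Scores are weekly from week 2, so late leavers carry values close to week 7. A reader might infer that LOCF freezes all dropouts at high entry scores. Table 1 does not support that; it is true only of early leavers. This stands.
- **The inputs are assumed.** The document gives no trajectory, timing or split by arm. The 25% is a planning allowance, and 10% versus 40% is an extreme split. This stands, so the figures show what could happen and do not predict what will.
- **The standard error.** A reader might infer that LOCF necessarily understates uncertainty. The calculations do not bear that out. What remains is that filled scores are treated as observed.
- **The per-protocol analysis gives a second view.** It does, but it is a completer analysis and does not handle missing values. When dropout rises with pain and differs by arm, complete cases gave 1.08–1.88 for a true 1.5.
- **It is a 60-patient pilot that may reach no conclusion.** This lowers the urgency but does not remove the point. The Objectives section states effectiveness hypotheses, and the fallback is to size the next trial. An effect read as 1.30 instead of 1.5 would raise that trial's size by (1.5/1.30)² = 1.33, about a third, at the same SD.
- **The analysis plan is not shown.** It may contain sensitivity analyses, so one cannot infer that none exist. LOCF, however, is a choice the article states, not a detail it leaves out.

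**Conclusion.** The point holds in conditional form. LOCF is the sole stated method, it rests on common use alone, and it can bias the primary week-7 comparison. The direction is toward the null with equal dropout and a true effect, and either way with unequal dropout. Equal dropout with no effect gives no bias.

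Under the linear, evenly spread illustration, the loss is about 0.2 of a true 1.5 points. The false differences of 0.31 and 0.47 are 21% and 31% of the planned 1.5. Late dropout gives less bias; early or pain-dependent dropout gives more. None of these sizes can be fixed from the document.

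This should be changed before the data are analysed. It does not invalidate the design: the 0.31 is about 0.4 of the full-data standard error of 0.79.

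**What to change.** In Statistical analysis, replace LOCF for the primary week-7 comparison with one of two methods of equal standing, named in advance:

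1. Multiple imputation by arm from the baseline and weekly NRS scores, followed by the between-group comparison. This is the smaller change to the plan. Pooling is simple for mean differences but less so for the rank tests and Duncan's procedure, so the pooled contrast should be named.
2. A likelihood-based repeated-measures model for NRS at weeks 2 to 7, with arm, visit, arm-by-visit and baseline NRS, and the week-7 contrasts as the result. Site is optional, since randomisation is not stratified by it. An unstructured covariance over six visits has 6 × 7/2 = 21 parameters, so a simpler structure should be pre-specified as fallback for 60 patients.

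Both assume that dropout depends only on recorded information, so a sensitivity analysis remains useful. LOCF can stay in that role only.

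The cost is revised wording and slightly more programming. No new data are needed.

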### Economic evaluation

Economic evaluation will be performed to assess cost-effectiveness of the three groups. The primary economic endpoint will be cost per quality-adjusted life year (QALY) gained, and secondary economic endpoints will cover such effectiveness parameters as cost per NRS. The primary analysis period will be 14 weeks and, if further estimation is needed, secondary analysis using regression-model or decision-modelling analysis to extrapolate cost and effect beyond the follow-up period will be performed. Treatment costs related to the clinical trial will be calculated by multiplying number of treatment sessions with unit cost, and unit costs will use national health insurance and medical institution cost data. Estimates of quality of life for QALYs will use the EQ-5D as the main assessment variable in the area under the curve method [34]. In the case that total time horizon is at least 12 months, the unit cost will be standardized using the Korean monetary unit (won) value as of 2013 and applying a discount rate of 5% in accordance with Korean HIRA economic evaluation guidelines. The analysis perspective of this study will be social and, in baseline analysis, representative values (e.g., average) of study parameters will be used. All available distribution and representative values of parameter estimates will be applied in probabilistic sensitivity analysis.

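### No baseline EQ-5D adjustment is specified for the QALY comparison, and the only adjustment rule in the plan waits for a significant baseline difference, so precision is lost

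*Protocol article*

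**What the plan says.** The Economic evaluation section of the protocol article states: "The primary economic endpoint will be cost per quality-adjusted life year (QALY) gained". It sets the horizon ("The primary analysis period will be 14 weeks") and the way QALYs are built: estimates of quality of life "will use the EQ-5D as the main assessment variable in the area under the curve method". For what is evidently the base case it adds that "in baseline analysis, representative values (e.g., average) of study parameters will be used". It names no covariate for the comparison of QALYs between arms.

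The Statistical analysis section holds the only baseline adjustment in the document: a secondary ANCOVA "adjusting for statistically significant between-group differences in baseline outcomes or covariant factors at baseline". Nothing links this rule to QALYs.

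Table 1 ("Time points of each assessment index") places the EQ-5D at weeks 0, 5, 7, 10 and 14, so the baseline value is already collected. The Abstract and the Objectives describe the cost-effectiveness analysis as exploratory.

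**The concern.** Baseline utility enters a QALY comparison in two ways. It is the first point of each patient's curve, and it predicts the later points. If arms differ by chance at week 0, part of that difference appears in the difference in mean area under the curve, although treatment had no part in it. With 20 patients per arm such differences are not small compared with the QALY gain that a 14-week horizon allows.

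Followed as written, the text leads to a comparison of averages, or at best to a covariate that enters only after a significant baseline test. That trigger does not serve the purpose. The value of a baseline covariate depends on how strongly it predicts the outcome, not on whether the arms happen to differ significantly on it.

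A ratio endpoint makes this matter more. When the QALY difference in the denominator is small or has the wrong sign, cost per QALY is hard to interpret. The Trial status section expects a full-scale trial to start after these data are analysed, so an imprecise QALY difference could carry forward.

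**Working it through.** The plan states no figure for EQ-5D or QALYs, so there is none to reproduce. Its sample size calculation concerns the NRS and does not bear on this point.

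**Inputs from the protocol.** EQ-5D at weeks 0, 5, 7, 10, 14 (Table 1); 14-week horizon; 20 patients per arm (Sample size); two-sided 5% level (Statistical analysis).

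**Assumptions, since the documents give none.** EQ-5D SD of 0.10–0.20, equal at all visits; correlation ρ of 0.3–0.7, equal between all visits; for scale, a utility gain of 0.05 at every visit after baseline.

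**Step 1: trapezoid weights.** Each visit carries half of each adjoining interval: 2.5, 3.5, 2.5, 3.5 and 2.0 weeks, which sum to 14. Baseline alone carries 2.5/14 = 17.9% of the area. The later visits carry 11.5 weeks.

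**Step 2: chance baseline difference between two arms.** SE = SD × √(2/20) = 0.316 SD, with 95% limits of ±1.96 × 0.316 = ±0.62 SD.

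**Step 3: carry-over into QALYs.** The expected shift per unit of baseline difference is (2.5 + 11.5ρ)/52:
- ρ = 0.3: 5.95/52 = 0.114
- ρ = 0.5: 8.25/52 = 0.159
- ρ = 0.7: 10.55/52 = 0.203

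**Step 4: standard errors.** The weighted sum of EQ-5D values has variance SD² × [(1−ρ) × 41 + ρ × 196], where 41 is the sum of squared weights and 196 = 14². The unadjusted SE of the QALY difference is the square root of this, divided by 52 and multiplied by √(2/20). The squared correlation of baseline with the area is r² = (2.5 + 11.5ρ)² / [(1−ρ) × 41 + ρ × 196]. Adjustment multiplies the SE by √(1−r²), ignoring the small cost of estimating one slope. At ρ = 0.5: r² = 8.25²/118.5 = 0.574, and √(1−0.574) = 0.65.

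| SD | ρ | SE of baseline difference | QALY shift, 1 SE | QALY shift, 95% limit | SE unadjusted | SE adjusted | Ratio |
|---|---|---|---|---|---|---|---|
| 0.10 | 0.3 | 0.032 | 0.0036 | 0.0071 | 0.0057 | 0.0044 | 0.77 |
| 0.15 | 0.5 | 0.047 | 0.0075 | 0.0148 | 0.0099 | 0.0065 | 0.65 |
| 0.20 | 0.7 | 0.063 | 0.0128 | 0.0251 | 0.0149 | 0.0075 | 0.51 |

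The ratio depends on ρ only, not on the SD.

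**Step 5: scale.** A gain of 0.05 at every later visit is worth 0.05 × 11.5/52 = 0.011 QALY.

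**Step 6: the trigger.** Under valid randomisation every baseline difference is due to chance, so a 5% test is significant in about 5% of pairwise comparisons at any sample size. At 20 per arm it needs a gap above about 0.62 SD (normal approximation). Smaller gaps go unadjusted, including those above 0.25 SD, which occur in about 43% of pairwise comparisons.

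**The case against.** The strongest reply is that this is read out of silence. The area-under-the-curve method describes how one patient's QALY is built, not how arms are compared; a regression of that area on arm and baseline is consistent with it; and the averages of the base case could be adjusted means. The article condenses a fuller protocol, and a health-economic plan that is not shown may name the covariate. The significance-triggered ANCOVA stands in a different section and is not said to govern QALYs.

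Much of this is right. A reader might infer that the plan commits itself to a raw comparison; the text never says so. What remains is that the one adjustment rule the document does state is poorly chosen, and the economic section puts nothing better in its place.

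Three further inferences also go too far:
- **Bias.** Randomisation makes the unadjusted difference unbiased on average. The loss is in precision and in accuracy for the sample actually drawn. The imbalance is already part of the unadjusted standard error and can be carried into the planned probabilistic analysis.
- **Trial size as the reason the trigger seldom fires.** The 5% rate is the significance level itself.
- **Ready reversal of the sign.** In the central case a one-SE shift of 0.0075 is below the assumed gain of 0.011; about 1.5 SE (0.011/0.0075) would be needed to cancel it. Of the combinations tabulated, only SD 0.20 with ρ = 0.7 gives a one-SE shift above that gain.

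The numbers also rest on assumed SDs and correlations. Baseline's direct weight is only 17.9%; the rest of the carry-over comes through ρ.

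**Conclusion.** The point holds as one of efficiency. The protocol specifies no baseline EQ-5D adjustment for QALYs, and its only stated rule is secondary and conditional on a baseline significance test. Across the assumed ranges, chance imbalance at the 95% limit is comparable with, and in part of the range more than twice, the 0.011 QALY taken as a yardstick (0.0251/0.011 ≈ 2.3). Adjustment reduces the SE by about a quarter to a half, equivalent to multiplying the sample size by about 1.7 (1/0.772²) to 3.9 (1/0.505²). These figures need EQ-5D SDs and correlations near those assumed; the direction of the gain needs only a positive correlation between baseline and later EQ-5D.

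Because the economic analysis is labelled exploratory and the estimator is not biased, this is a recommended improvement that costs nothing, not a flaw that invalidates the analysis.

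**What to change.** Add one sentence to Economic evaluation: the between-arm difference in QALYs will be estimated by linear regression of each patient's 14-week EQ-5D area under the curve on treatment arm and week-0 EQ-5D, whatever any baseline comparison shows. State that this adjusted difference is used in the cost-per-QALY base case, and that the adjusted estimate and its uncertainty enter the probabilistic sensitivity analysis. Make clear that the significance-triggered ANCOVA does not govern QALYs.

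The cost is that sentence and one degree of freedom. The covariate is already in the assessment schedule, so no visit, questionnaire or patient is added.

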### Data collection and management

Paper CRFs will be used and a standard operating procedure (SOP) for CRF entry will be prepared. Investigators and the contract research organization (CRO) at the lead study site (Pusan National University Korean Medicine Hospital) will educate outcome assessors and investigators at each site regarding CRF entry, electronic data conversion, and SOP. Double data entry will be allowed in CRF outcome measurement data, with data entered once at each study site, and once at the lead organization and CRO, respectively. After confirming whether electronic data conversion using double entry is accurate, data access will be blocked to all researchers except statisticians.

### Adverse events

Physicians will monitor and record any unexpected or unintended patient reaction to *Chuna*, usual care, or its combination at each visit. Adverse events (AEs) associated with *Chuna* will include, but not be limited to, AEs anticipated from previous reports of manual therapy and will stay open to all possibilities taking into consideration other potential, unknown AEs. Physicians will rate the causal relationship between each treatment method and AE occurrence on a 6-point scale (1 = definitely related; 2 = probably related; 3 = possibly related; 4 = probably not related; 5 = definitely not related; and 6 = unknown), and all AEs will be categorized into three levels using the Spilker classification (mild (1) = not needing additional intervention, nor significantly inhibiting to the normal lifestyle (function) of the participant; moderate (2) = significantly inhibiting to the normal lifestyle (function) of the participant, and may need additional intervention, recovering afterwards; and severe (3) = severe AE requiring intensive intervention, and leaving sequelae). In the case of “serious adverse event (SAE)” during study duration, unblinding is permissible and the relevant Institutional Review Board (IRB) and main study site (Pusan National University Korean Medicine Hospital) will be informed and will decide whether the trial will continue or be terminated. In the event that a subject suffers direct injury associated with the clinical trial, the subject may receive appropriate medical action as seen fit by the subinvestigator, and damage compensation will follow prespecified clinical research insurance clauses. All study participants will be provided with an emergency contact number to the principal investigator or subinvestigator for any questions, medical issues or research-related diseases during the study and accordingly receive requested services.

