### Objectives

Objective evaluation of the comparative effectiveness, safety, and economic evaluation of *Chuna* manual therapy for application in cost-effective, evidence-based practice are important issues both for the Korean medicine sector and for national health services improvement. High-quality RCTs are warranted for rigorous assessment of *Chuna* effectiveness, safety, and cost-effectiveness. The hypotheses of this study are as follows: (1) *Chuna* manual therapy will be more effective and safer than (or equally safe as) conventional usual care in nonacute LBP patients and (2) concurrent treatment consisting of *Chuna* manual therapy and usual care will be more effective than *Chuna* alone or conventional usual care alone in nonacute LBP patients. Therefore, the objectives of this pCRN (pilot *Chuna* Research Network) study are to investigate the following in nonacute LBP patients: (1) the comparative effectiveness and safety of *Chuna* manual therapy compared to conventional usual care through comparison of pain, functionality, quality of life parameters and adverse events, (2) the effectiveness and safety of a concurrent treatment consisting of *Chuna* manual therapy and usual care, which is reflective of actual clinical practice, through comparison of two single treatment groups of *Chuna* manual therapy and usual care, and a combined treatment group of *Chuna* manual therapy with usual care and (3) costs and effectiveness (utility) data of the three groups for exploratory cost-effectiveness analysis (economic evaluation). However, if the current sample size deters this pilot study from reaching a definite conclusion regarding aims (1), (2), and (3), the main objectives of this preliminary study will be to determine a sample size appropriate for statistical testing in future large-scale studies and to assess the feasibility of a full-scale multicenter trial.

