### Blinding

As blinding of physicians and participants to allocation of treatment groups is impossible in the current design due to dissimilarity of interventions, only outcome assessors, statistician and data analysts will be blinded. The outcome assessors will not participate in treatment and a research nurse or KMD blinded to allocation will conduct outcome assessment in a separate room after treatment and will not attempt to become knowledgeable of allocation. The patient will also be cautioned against informing the outcome assessor of treatment allocation prior to each assessment. The electronic data transferred to statistician and data analysts will not contain information on treatment allocation.

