#### Combined Chuna manual therapy and usual care

The combined treatment group of *Chuna* manual therapy and usual care will receive both treatments in the same method, frequency, session length, total duration, and number of sessions of each treatment as that of the other two groups.

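### The adverse-event rule is worded as a reaction to treatment, so unblinded physicians judge cause before recording; this conflicts with the protocol's own causality scale and can distort the between-arm safety comparison

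*Protocol article*

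**What the plan says.** - **Recording rule (Adverse events).** "Physicians will monitor and record any unexpected or unintended patient reaction to" Chuna, usual care or the combination, at each visit. The article gives no other statement of what is to be recorded.
- **Causality (same section).** Physicians rate each event against each treatment method on six points. Point 4 is probably unrelated, and the scale ends "5 = definitely not related; and 6 = unknown". Severity is graded for all adverse events.
- **Anticipated events (same section).** Those associated with Chuna "will include, but not be limited to, AEs anticipated from previous reports of manual therapy", and the description "will stay open to all possibilities taking into consideration other potential, unknown AEs". Usual care has no matching sentence, although the Usual care section includes oral medicines.
- **Blinding.** "As blinding of physicians and participants to allocation of treatment groups is impossible". Only outcome assessors, the statistician and the data analysts are blinded.
- **Use of the data.** Hypothesis 1 in Objectives is that Chuna "will be more effective and safer than (or equally safe as) conventional usual care". Objectives 1 and 2 compare safety between arms. Data monitoring and safety monitoring takes the number and percentage of participants with adverse events as the summary, with all serious events included.
- **Schedule.** Table 1 has one adverse-event row for all three arms: baseline, every treatment visit, and weeks 7, 10 and 14.

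**The concern.** A reaction to a treatment is, by meaning, something the treatment caused. A rule in those terms puts the attribution step before the recording step, and gives it to people who know the arm. In an open-label comparison the usual protection is the reverse order: record every event first, then judge cause. The between-arm count then does not depend on that judgement.

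The rule also pulls against the causality scale beside it. A physician who follows the rule would rarely have anything to grade as definitely unrelated. A physician who takes the cue from the scale would record everything. Four hospitals enrol, so both practices could occur in one trial.

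At stake is the percentage of participants with an adverse event, which is the planned safety measure. The Discussion also offers the pilot's safety results as preliminary information for the later full-scale trial, so a distorted count could carry forward.

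**Working it through.** The protocol gives no adverse-event rate or recording probability, so there is no figure to reproduce. The check is first one of wording, then an illustration on assumed inputs.

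**Step 1: rule against scale.** The rule admits events that are reactions to treatment. Of the six grades, 4 (probably unrelated) and 5 (definitely unrelated) describe events that are not reactions in the physician's judgement, and 6 (unknown) describes events whose status as reactions is undecided. Three of the six grades therefore apply to events that the literal rule does not clearly admit. The two statements cannot both be followed to the letter.

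**Step 2: who applies the rule.** Recording and causality rating are assigned to physicians. The Blinding section says that physicians cannot be blinded, and rating relatedness to each treatment method requires knowing what was given. The blinded outcome assessors are not named in the recording rule.

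**Step 3: where the result goes.** The recorded events form the numerator of the percentage of participants with adverse events. That percentage serves hypothesis 1 and objectives 1 and 2.

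**Step 4: what differential recording would do (assumed inputs).** Let the true risk p be equal in two arms, and let s1 and s2 be the probabilities that an affected participant is recorded.

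- Apparent risk ratio = (p × s1)/(p × s2) = s1/s2.
- Apparent risk difference = p × (s1 − s2).
- The planned arm size is 20 (Sample size section). The range for p is assumed to be 0.10 to 0.40.

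| s1 vs s2 | Apparent RR | Apparent RD, p = 0.10 | Apparent RD, p = 0.40 |
|---|---|---|---|
| equal | 1.0 | 0 | 0 |
| 0.9 vs 0.6 | 0.9/0.6 = 1.5 | 0.10 × 0.3 = 0.03 | 0.40 × 0.3 = 0.12 |
| 1.0 vs 0.5 | 1.0/0.5 = 2.0 | 0.10 × 0.5 = 0.05 | 0.40 × 0.5 = 0.20 |

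In the last row the expected counts per 20 run from 2 versus 1 (p = 0.10) to 8 versus 4 (p = 0.40, that is 40% versus 20%). Swapping the arms reverses the sign, with ratios of 0.67 and 0.5. The illustration shows what unequal recording can do. It is not evidence that recording will be unequal.

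**The case against.** The strongest reply is that the section, read whole, intends to record events and then rate them. It has grades for unrelated and unknown cause, it grades all adverse events for severity, and the safety summary is not limited to related events. On this view the recording sentence is merely loose. That stands as far as intent goes: a reader might infer that unrelated events are excluded outright, and the text does not support so strong a claim. What remains is that the only sentence telling physicians what to record uses the narrower definition.

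Three further inferences are tempting, and the documents do not support them:

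- **A prompt list used only for Chuna.** None is described. The Chuna sentence is an open-ended statement of scope, and the recording rule names all three regimens. What is uneven is only that anticipated events are described for one treatment.
- **Twice as many recording opportunities in the combined arm.** That arm "will receive both treatments in the same method, frequency, session length, total duration, and number of sessions of each treatment", but nothing says that the two treatments mean separate visits or separate enquiries. Table 1 gives the combined arm the same weekly frequency as each single arm, and one adverse-event row for all.
- **That the physicians are the treating ones.** The text says only physicians. The inference is reasonable, but the point does not need it, because physicians as a group are unblinded.

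There are also safeguards. An outside contract research organisation cross-checks safety data, case report forms and source documents, and form entry follows a standard procedure with training. These limit the risk. They do not settle which events should be written down, and a cross-check can find only what someone recorded.

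Finally, elicitation details are commonly left to the full protocol or the case report form. That is fair for checklists and form layout. It does not answer a rule that is stated in the article and conflicts with the scale beside it.

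**Conclusion.** The point holds as an internal inconsistency with a practical consequence. The stated rule defines a recordable event by attribution, the attribution is made without blinding, and the rule disagrees with the causality scale in its own section. The one-sided description of anticipated events adds to the risk of unequal ascertainment.

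A reader might go further and conclude that the safety comparison is biased. The documents do not show that. Fuller wording for Chuna could raise its count, while provider belief could lower it, and the common schedule may keep recording equal. The supportable statement is that the comparison can be distorted, with size and direction unknown. The spurious differences of 3 to 20 percentage points in the working rest wholly on assumed risks of 10% to 40% and assumed recording probabilities. The change is worth making because between-arm safety is a stated hypothesis and the correction is cheap.

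**What to change.** In the Adverse events section:

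- Replace the recording rule with one that covers every untoward medical occurrence after randomisation, whatever its suspected cause.
- Elicit events with the same question in all three arms, at the adverse-event visits already in Table 1.
- Rate causality on the existing six-point scale only after the event has been recorded.
- If anticipated events are listed, list those of manual therapy and those of usual care together, and use the same list in every arm.

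In Data monitoring and safety monitoring, state that the between-arm comparison uses all-cause adverse events, and that physician-rated relatedness is reported separately.

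The cost is protocol wording, a matching edit to the case report form, and more minor unrelated events recorded. No visit is added and no treatment changes. A participant-completed checklist would be one way to standardise the enquiry, but it is optional.
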